#### Secondary Outcome Measures

• Rates of ≥ CIN2 and hr-HPV respectively at initial screen in control and safety/intervention arms;

• Rates of incident ≥ CIN2 at two years in control arm and at four years in intervention arm;

• The total estimated cost per woman screened and the total estimated cost per quality-adjusted life-year gained for each technology;

• Clearance of hr-HPV infection in women who are hr-HPV-positive and cytology negative at initial screen.

The primary outcome analysis will be a comparison of histologically confirmed ≥ CIN3 between the intervention and control arms. Rates of lesion occurrence will be calculated using person-time denominators for the different study intervals and compared via Kaplan-Meier plots[26]. Rates will be calculated for specific age groups within the study. Significance testing will be based on Poisson statistics and performed at the 5% level (2-sided). Analysis will also be performed using logistic regression to permit control of potential confounding factors since for some comparisons balance may not be assured by randomization. The primary comparison of disease rates between test negative groups (at entry screen) will not control for potential confounding factors since they are not balanced by randomization and the tests may select for different characteristics. Covariate-adjusted analyses will be performed to determine the extent to which any difference is explicable by potential confounders (e.g., age and sexual behaviour).

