## Background

Cervical cancer screening using cervical cytology (the Pap smear) has been an extremely successful public health intervention, achieving reductions in cervical cancer incidence of up to 80% where practiced effectively[1]. However, the Pap smear was introduced over 50 years ago and studies have now proven it has significant limitations. Data from some jurisdictions indicate that cervical cancer rates have reached a nadir, and meta-analyses indicate that the sensitivity of a single Pap test to detect cervical intraepithelial neoplasia (CIN) or invasive cervical cancer is less than 60%[2,3].

There is now ample evidence that infection with high-risk types of the Human Papillomavirus (hr-HPV) is a requisite intermediate step for the development of cervical cancer and its precursors[4,5]. On this basis, it has been proposed that testing for the presence of hr-HPV could improve cervical cancer screening. HPV testing is recommended for follow up of abnormal cytology in women over the age of 30 and for the surveillance of patients after colposcopic treatment for CIN[6]. When used as a primary screening tool in cross sectional studies, it has been demonstrated that hr-HPV testing has a higher sensitivity and negative predictive value (NPV) for CIN2 or worse (≥ CIN2) detection than either the conventional Pap smear or liquid based cytology (LBC), albeit with a lower specificity and positive predictive value (PPV)[7-12]. In recognition of this, one approach for screening would be to use hr-HPV testing as a **single primary screening test **with cytology reserved only for the triage of women having a positive test, especially following the advent of HPV vaccination[12,13]. This would offer several advantages over combined testing:

• Screening would be undertaken with the test having higher *sensitivity *(hr-HPV testing);

• 85-90% of women would be returned immediately to routine screening with a negative hr-HPV test without incurring the cost of cytology, which would be reserved only for those with a positive hr-HPV;

• The high-volume screening of samples would be undertaken with a non-subjective test that can be automated, while the subjective, labour-intensive test would be restricted to high-risk samples that could be examined with greater vigilance because of the reduced number to be interpreted;

• It represents a more robust screening approach that could serve the additional purpose of post-vaccination surveillance in the population[13];

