This paper describes the design and preliminary screening results of the HPV FOCAL Trial. The primary objective of the HPV FOCAL trial is to establish the efficacy of hr-HPV testing followed by liquid based cytology (LBC) triage of hr-HPV-positive women compared to LBC followed by hr-HPV triage for cervical cancer screening with ≥ CIN3 as the outcome, through a comparison of the estimated decreases in cervical intraepithelial neoplasia (CIN 2/3) that can be achieved by each screening modality in successive screening rounds. The secondary objectives of this trial are to establish the appropriate screening interval for hr-HPV negative women, using the current standard of a 2-year recall interval for cytology negative women as the benchmark of acceptable risk in British Columbia; to establish the appropriate clinical follow-up for hr-HPV positive women; and to establish the cost-effectiveness of hr-HPV testing for primary screening, all within the context of a population based Canadian cervical cancer screening program. The results of this trial will demonstrate whether or not the use of hr-HPV testing as a single primary screening test within a population based cervical cancer screening program will be able to provide further reductions in the incidence of cervical cancer and its precursor lesions, allow the screening interval to be extended, and improve the cost-effectiveness of cervical cancer screening.

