**Figure 1 F1:**
[figure not shown]
**HPV FOCAL: a three-armed, RCT over a four year period**.

**Control arm**: LBC at entry and again at two years; ASCUS cases are triaged with hr-HPV testing; combined LBC and hr-HPV at four years (exit screen) among those with initial negative results.

**Two Year Safety Check arm**: hr-HPV at entry; LBC at two years (exit screen) in those with initial negative hr-HPV results with LBC triage of hr-HPV positives at either round.

**Four Year Intervention Arm**: hr-HPV at entry with LBC triage of hr-HPV positives; combined hr-HPV and LBC at four years (exit screen) among those with initial hr-HPV negative results.

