Important design elements in HPV FOCAL include the use of LBC (a more universal cytology format in North America) as opposed to conventional cytology; the use of FPs as study collaborators to recruit participants; blinded analysis of cytology and pathology results with respect to hr-HPV status; use of a single laboratory for cytology analysis; inclusion of a two year safety arm and standardized colposcopy protocols. The use of LBC is of particular relevance because of the ability to use the sample for reflex testing. LBC, which involves taking a sample and placing it into a vial with liquid, and then producing a slide for examination from a suspension of the cells has been compared to conventional cytology in many studies[27]. Studies have reported higher sensitivity with LBC compared to conventional smears, as well as a greater proportion of adequate specimens for evaluation. However, there remains a divergence of opinion on the advantages of LBC over conventional cytology, and a recent RCT found that LBC had equivalent sensitivity for ≥ CIN2 lesions relative to conventional Pap, but had a lower rate of unsatisfactory smears when compared with the latter[28]. In a cluster randomized trial involving over 89,000 women, Siebers et al. [29] found that LBC did not perform any better than well-performed conventional Pap smears for the detection of cervical cancer precursors. Despite the differences in results, LBC has been widely adopted worldwide and particularly in North America as a part of cervical cancer screening programs due to opportunities for automation, improved costs and single specimen collection for HPV and other molecular tests. The HPV FOCAL trial is well positioned to examine the contribution of LBC with respect to primary HPV testing and inform the discussion internationally. These findings would be directly relevant to cervical cancer screening programs worldwide as they consider the respective roles of LBC and HPV testing in their future program delivery.

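### The secondary comparison of ≥CIN2 at two years (control) with ≥CIN2 at four years (intervention) changes the exit test along with the interval, and nothing planned separates the two

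*Protocol article*

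**What the plan says.** The outcome, in the protocol article under Secondary Outcome Measures, is "Rates of incident ≥ CIN2 at two years in control arm and at four years in intervention arm".

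The Figure 1 legend fixes the test at each of these screens. In the control arm it is "LBC at entry and again at two years; ASCUS cases are triaged with hr-HPV testing". In the intervention arm it is "combined hr-HPV and LBC at four years (exit screen) among those with initial hr-HPV negative results".

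The Background states what the interval comparison is for: the appropriate interval for hr-HPV-negative women is to be judged "using the current standard of a 2-year recall interval for cytology negative women as the benchmark of acceptable risk in British Columbia".

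The analysis text under Secondary Outcome Measures specifies rates with person-time denominators, Poisson testing at the two-sided 5% level, and covariate-adjusted analyses for factors such as age and sexual behaviour. It does not mention the test used at the exit screen.

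**The concern.** A rate of detected lesions is the product of two things: the lesions present, and the share of them that the screen finds and sends to biopsy. The interval objective concerns the first. In this comparison both differ between the arms, and the exit test is fixed by the arm, so no covariate model could separate them even if one were planned.

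The direction of the detection part follows from the article's own account. The Background says that hr-HPV testing has higher sensitivity for ≥CIN2 than conventional or liquid-based cytology. A four-year screen that includes it should therefore find a larger share of the lesions present than a two-year LBC screen. An hr-HPV-negative result that protects for four years as well as a negative smear does for two could then appear to protect less well, and the interval conclusion could be wrong for that reason.

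**Working it through.** The article gives no expected rate and no power for this comparison, so there is no figure of the plan's own to reproduce. The 11,000 per arm does not enter the check.

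**Which comparisons are matched (Figure 1 legend)**
- Control and intervention at four years: control has "combined LBC and hr-HPV at four years (exit screen) among those with initial negative results", the same co-test as intervention. Matched.
- Control and safety check at two years: the safety arm has "LBC at two years (exit screen) in those with initial negative hr-HPV results", the same primary test as control. Matched.
- Control at two years and intervention at four years: LBC against LBC plus hr-HPV. Not matched.

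**Inputs for the size**
- Cytology: the only figure is in the Background, "the sensitivity of a single Pap test to detect cervical intraepithelial neoplasia (CIN) or invasive cervical cancer is less than 60" per cent. This bounds a single Pap test for CIN or cancer in general and is not an LBC estimate for ≥CIN2. I therefore assume LBC sensitivity of 0.50 to 0.80.
- Co-test: no figure is given. I assume 0.95, with a range of 0.85 to 1.00.

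**Detection-only ratio at equal true risk** = co-test sensitivity / LBC sensitivity, if every lesion flagged is biopsied.

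| LBC | co-test 0.85 | co-test 0.95 | co-test 1.00 |
|---|---|---|---|
| 0.50 | 1.70 | 1.90 | 2.00 |
| 0.60 | 1.42 | 1.58 | 1.67 |
| 0.70 | 1.21 | 1.36 | 1.43 |
| 0.80 | 1.06 | 1.19 | 1.25 |

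For example, with 10 lesions per 1,000 women in both arms, LBC at 0.60 finds 6.0 and a co-test at 0.95 finds 9.5; 9.5/6.0 = 1.58. With the same test in both arms the ratio is 1.00.

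**Net ratio with lesions missed at entry.** Let P be the prevalence at entry and λ the onset rate per year, the same in both arms. Assume entry and co-test hr-HPV sensitivity 0.95, LBC 0.60, and independent misses at successive screens.
- Control rate = 0.60 × [(1 − 0.60)P + 2λ] / 2
- Intervention rate = 0.95 × [(1 − 0.95)P + 4λ] / 4

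With P = 0.005 and λ = 0.002 (both assumed):
- Control: 0.60 × 0.006 / 2 = 0.00180
- Intervention: 0.95 × 0.00825 / 4 = 0.00196
- Planned ratio: 1.09
- Ratio with the four-year screen read by LBC: 1.09 × 0.60/0.95 = 0.69

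With P = 0.01 and λ = 0.002:
- Control: 0.60 × 0.008 / 2 = 0.00240
- Intervention: 0.95 × 0.0085 / 4 = 0.00202
- Planned ratio: 0.84
- Ratio with the four-year screen read by LBC: 0.84 × 0.60/0.95 = 0.53

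In the first case the matched ratio equals the true ratio of lesions per person-year, (0.00825/4)/(0.006/2) = 0.69, because the common sensitivity cancels. The planned ratio lies on the other side of 1.

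**The case against.** **The size is not known.** A reader might combine the Background's 60% figure with a co-test near 0.95 and conclude that the intervention arm can look up to about 60% worse. The documents do not support that. The 60% is an upper bound for Pap testing, so it allows ratios above 1.58. The Discussion reports divided evidence on LBC, with some studies finding higher sensitivity and one trial finding that "LBC had equivalent sensitivity for ≥ CIN2 lesions relative to conventional Pap". The co-test figure is not in the article at all. This objection stands.

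**The extra yield depends on referral.** Every group listed under Colposcopy has abnormal cytology. If women who are hr-HPV positive with normal cytology at exit are not referred, the added test brings few extra lesions and the ratio moves towards 1.00. The listed groups are described as the major ones and point to Figure 1, which is not shown. This stands as a limit on the size.

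**The net effect may be nil or reversed.** Lesions missed by entry LBC raise the control rate at two years, and the planned comparison is of person-time rates, not raw counts. A reader should not infer that the intervention arm will look worse overall. However, missed lesions are part of the risk that the objective asks about, and the detection factor multiplies the result whatever they are, so they do not remove it.

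**Scope and direction.** This is one secondary outcome, and the detection effect does not by itself make four years look falsely safe. Both points are fair. Rejecting an adequate interval would still be a wrong answer to the stated objective.

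**The SAP may cover it.** A breakdown by triggering test could be there. The mismatch itself, though, is fixed by the outcome and the screening schedule as the article states them.

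**Conclusion.** The point holds as a confounding of exit test with interval in this one secondary outcome. Its detection part works against the four-year hr-HPV interval, and no planned adjustment addresses it.

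Its size cannot be taken from the documents. As an illustration, at equal true risk, with a co-test at 0.95 and all flagged lesions biopsied, the detection-only ratio is 1.90 to 1.19 for LBC sensitivity of 0.50 to 0.80. These sensitivities are assumptions. The ratio shrinks if exit hr-HPV positivity alone does not lead to colposcopy. The net person-time ratio also depends on lesions missed at entry; under the assumed inputs it was 1.09 in one case and 0.84 in another.

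The comparison of cumulative ≥CIN3 between control and intervention, and the two-year comparison of control with safety check, are test-matched and not touched by this.

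**What to change.** Keep the planned rate and add a test-matched analysis of this outcome beside it:
- In the intervention arm, count only ≥CIN2 in women whose exit LBC, with hr-HPV triage of ASCUS, met the referral rule applied in the control arm at two years.
- ASC-US that is hr-HPV negative and later persists cannot be classified from a single exit sample. Handle it the same way in both arms, or leave it out of both, and say which.
- Report separately the lesions found only through the exit hr-HPV result.
- The listed referral groups for AGC and for ASC-H or ≥LSIL specify hr-HPV positive or not done. Report how many women met the control rule on exit LBC but had no colposcopy, since their lesions would be missing from the matched count.
- Base the interval conclusion on the test-matched rate.

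Both results exist for each co-tested exit sample, and the Discussion says that cytology is read blind to hr-HPV status. The change needs a derived variable, a rule for persistent ASC-US and a few sentences in the analysis plan. It adds no visit or test and changes no patient's management. The downside is fewer counted events and so a less precise rate.

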### Statistical Considerations

#### Sample Size

The planned intake sample size is 11,000 women per arm (33,000 total). Power calculations were performed using the nQuery Advisor, version 2, software package. Rates of hr-HPV infection and associated histologically proven disease were based on results from the HART study[9], prevalence rates from the CCCaST trial conducted in Quebec and Newfoundland[8,25]. Sample sizes were based on requiring at least an 80% power to detect relative differences (alternative hypothesis) of 20% in the outcome comparisons for intervention versus control at four years and control versus safety check arms at two years.

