### Analysis

#### Primary Outcome Measures

• Control and intervention arms: Cumulative incident ≥ CIN3 detected up to and including four years in both the control arm and the intervention arm

• Control and safety check arms: Incident ≥ CIN2 detected at two years. If the number of ≥ CIN2 in the safety-check group exceeds 0.8 times that in the control arm at the 2 year screen, then the trial will conclude and women in the four year intervention arm will be recalled at two years for their exit screen.

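### Person-time rates are the wrong scale for the secondary comparison of ≥ CIN2 at two years (control) with four years (intervention): they halve the risk ratio at recall

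*Protocol article*

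**What the plan says.** Four statements in the protocol article bear on this point.

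- **Objective** (Background, last paragraph). A secondary objective concerns how long women with a negative hr-HPV test can wait before they are screened again. Its yardstick is given in these words: "using the current standard of a 2-year recall interval for cytology negative women as the benchmark of acceptable risk in British Columbia".
- **Outcome** (Secondary Outcome Measures). The matching item in the list is "Rates of incident ≥ CIN2 at two years in control arm and at four years in intervention arm".
- **Scale** (same section, below the list). "Rates of lesion occurrence will be calculated using person-time denominators for the different study intervals and compared via Kaplan-Meier plots".
- **Test** (same section). Poisson statistics, two-sided, at the 5% level. Logistic regression is added with a stated purpose: "Analysis will also be performed using logistic regression to permit control of potential confounding factors".

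The primary outcome is worded differently, as a cumulative quantity over the same period in both arms: "Cumulative incident ≥ CIN3 detected up to and including four years in both the control arm and the intervention arm".

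**The concern.** The benchmark is the risk that a cytology-negative woman has accumulated when she returns at two years. The question for the longer interval is whether an hr-HPV negative woman returning at four years has accumulated more than that. Both are cumulative risks, one over 24 months and one over 48.

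A person-time rate divides each risk by the length of its own interval. The four-year risk is divided by four and the two-year risk by two, so the longer interval is credited with its length, although its length is what is in question. If the sentence on person-time is applied to this outcome, a four-year risk close to double the benchmark gives a rate ratio close to 1. A four-year risk equal to the benchmark reads as a halving. A reader weighing an extension of the interval could be misled about how the new schedule stands against the current one.

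**Working it through.** **Inputs from the protocol article**

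- Intervals: 2 years (control) and 4 years (intervention), from the Secondary Outcome Measures.
- Planned size: 11,000 women per arm, from Sample Size.
- Negative at entry: 1908/2019 in control (Table 3) and 1854/2012 in intervention (Table 4). Applied to 11,000, these give about 10,395 and 10,136 women.

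**Input assumed.** The article gives no two-year ≥ CIN2 risk in cytology-negative women. I take 0.5% for illustration and show the range 0.2% to 1.0%.

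**The plan's own figure.** The 11,000 per arm cannot be reproduced, because the control event rate behind it is not stated. It is used here only to count women. The Sample Size section bases power on the four-year and two-year equal-length comparisons and does not mention this contrast.

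**Step 1: the factor.** Let R2 be the control risk through the 2-year recall and R4 the intervention risk through the 4-year recall.

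Rate ratio = (R4/4) / (R2/2) = 0.5 × R4/R2

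| Risk ratio at recall, R4/R2 | Person-time rate ratio |
|---|---|
| 1.0 | 0.50 |
| 1.5 | 0.75 |
| 1.9 | 0.95 |
| 2.0 | 1.00 |

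No event rate enters the formula. If cases leave person-time in mid-interval instead of at recall, the ratios change by at most 0.005.

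**Step 2: what a rate ratio of 1 means.** With the same constant hazard in both groups, the risk ratio at recall is (1 − e^(−4λ)) / (1 − e^(−2λ)). For λ from 0.001 to 0.005 per year this is 1.998 to 1.990. Equal rates therefore mean almost twice the risk at recall.

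**Step 3: an illustration with R2 = 0.5% and R4 = 0.95%, all women returning.**

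- Expected cases: 10,395 × 0.005 ≈ 52 in control and 10,136 × 0.0095 ≈ 96 in intervention.
- Rates: 5/2 = 2.50 and 9.5/4 = 2.375 per 1,000 woman-years, ratio 0.95.
- Standard error of the log ratio: √(1/52.0 + 1/96.3) ≈ 0.172.
- Rate ratio 0.95, 95% CI 0.68 to 1.33. A two-sided 5% test is significant in about 6% of trials.
- Risk ratio at recall from the same cases, with the same standard error: 1.9, 95% CI 1.9 × e^(±1.96 × 0.172) = 1.36 to 2.66. It is significant in about 96% of trials.

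**Step 4: the range, with the true risk ratio kept at 1.9.** For R2 from 0.2% to 1.0%, the rate test is significant in 5% to 7% of trials. The risk comparison is significant in about 66% to 100%, or about 56% to 99.7% if 80% of women return.

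**The case against.** The strongest reply is that the article never says this contrast will be a ratio of person-time rates.

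- The person-time sentence directly follows the sentence on the primary ≥ CIN3 analysis, where follow-up is four years in both arms.
- In the same list, the rates of ≥ CIN2 and hr-HPV at the initial screen must be proportions, since no person-time has accrued. The two- versus four-year item is worded in the same way and could also mean proportions.
- Kaplan-Meier plots display cumulative risk, and logistic regression has no time denominator. Either could show a near-doubling.

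These points stand as reasons for caution, but they do not remove the problem. The person-time sentence speaks of lesion occurrence in general and of different study intervals. Nothing exempts the one listed comparison whose intervals are unequal, and nothing names a risk-at-recall contrast. Logistic regression is given for confounder control, and the plots are not assigned to the interval question.

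The exit tests also differ: LBC at two years in control, and combined hr-HPV and LBC at four years in intervention. This may raise detection in the intervention arm. It is a separate influence of unknown size and does not correct a fixed factor of one half.

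Some stronger readings are tempting but go beyond the document:

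- *That this analysis alone decides whether the interval is extended.* No deciding test is named, and the Discussion also links interval extension to the two-year safety check arm.
- *That the lack of a non-inferiority margin is an error.* An analysis plan that is not shown may hold it.
- *That lesions are found only at scheduled screens.* The Colposcopy section refers women with persistent ASC-US that was initially hr-HPV negative, which implies detection after repeat testing.
- *That counts will be low.* No ≥ CIN2 rate is given.

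**Conclusion.** The concern holds for one secondary comparison. If the stated person-time and Poisson rule is applied to ≥ CIN2 at two years in control and at four years in intervention, the result is half the risk ratio at recall. That is the wrong scale for an objective whose benchmark is risk at the two-year recall.

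The factor of one half assumes that women are recalled on schedule and that the control figure uses follow-up to 24 months only. It needs no assumption about event rates. The case counts and percentages of significant trials do rest on the assumed two-year risk of 0.2% to 1.0%.

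A reader might infer that the trial's main result is biased. It is not: the primary ≥ CIN3 comparison covers four years in both arms, and the safety comparison covers two years in both. The point is worth correcting because a stated method would mislead and the correction is cheap, but it does not threaten the trial's primary conclusion.

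**What to change.** For the interval objective, state that the comparison is the cumulative risk of ≥ CIN2 per 1,000 entry-negative women through the recall screen: 48 months in intervention against 24 months in control. Report it as a risk ratio and a risk difference, each with a confidence interval. Limit person-time rates and Poisson rate tests to comparisons of equal length, or present them as description. If a Kaplan-Meier estimate or a logistic model is to supply the risks, assign it to this contrast by name.

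The cost is a small change in analysis wording and the loss of a single rate scale across all comparisons. No new data, visits or participants are needed.

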### Randomization and Blinding

A database has been developed specifically for the HPV FOCAL trial. Randomization occurs through this database when samples are received at the laboratory. At the time of randomization a Study Identification Number (SIN) is allocated to the participant. Samples are stratified by age and simple equal (1/3 probability) random allocation occurs at the laboratory. Upon randomization, study staff label and batch the specimens for initial processing (hr-HPV or LBC).

FPs and participants are blinded to study arm allocation. Participant results are communicated from the BCCA to the FP office as soon as they are known. If the participant's initial screening results (hr-HPV or cytology) are "negative" the report states "within normal limits". The report also states that the recommended follow-up for that participant will be communicated to the FP in two years' time. This ensures blinding is maintained for as long as possible and prevents any bias that may potentially occur from knowledge of negative results. If the screening results are hr-HPV and/or cytology positive, the results are communicated from the BCCA to the FP along with the recommended follow-up.

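### The screening-interval objective is a no-worse-than question, but the only inference stated for lesion rates is a two-sided difference test, which does not control the error of accepting a risk above the benchmark

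*Protocol article*

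**What the plan says.** The objectives paragraph that closes the Background makes the appropriate interval for hr-HPV-negative women a secondary objective, "using the current standard of a 2-year recall interval for cytology negative women as the benchmark of acceptable risk in British Columbia". The outcome that matches it, under Secondary Outcome Measures, is "Rates of incident ≥ CIN2 at two years in control arm and at four years in intervention arm".

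The analysis text in the same section calculates lesion rates on person-time denominators, shows them as Kaplan-Meier plots and adds logistic regression for confounders. It compares the groups that were test-negative at entry without adjustment. On inference it says: "Significance testing will be based on Poisson statistics and performed at the 5% level (2-sided".

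Two other places might have supplied a criterion, but they concern different comparisons. The 0.8 rule under Primary Outcome Measures concerns safety check versus control at two years. The Sample Size section requires at least 80% power for "relative differences (alternative hypothesis) of 20% in the outcome comparisons for intervention versus control at four years and control versus safety check arms at two", the last figure being in years. Neither covers four years after a negative hr-HPV test against two years after negative cytology.

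**The concern.** A ceiling of acceptable risk poses a one-directional question: is the four-year risk no higher than the benchmark? The harmful error is to accept the longer interval when its risk is above the ceiling. A two-sided test of no difference limits a different error, that of declaring a difference where none exists. It sets no limit on the chance that a real excess goes unflagged, and that chance grows as events become fewer, for example with poor attendance at the exit screen.

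The Background says the results will show whether the screening interval can be lengthened, so the conclusion would inform policy. The mismatch does not depend on the person-time denominators or on the different tests used at exit. It would remain with plain cumulative risks and identical exit tests.

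**Working it through.** **Inputs.** From the article: "The planned intake sample size is 11,000 women per arm (33,000 total"); equal allocation; 94.5% cytology-negative at entry in control and 92.1% hr-HPV-negative in intervention (Preliminary Findings); two-sided 5%. Assumed, because the article gives no figure: a two-year ≥ CIN2 risk in cytology-negative women of p = 0.2, 0.3, 0.5 or 1.0%.

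**1. The plan's own figure.** The sample size cannot be reproduced, because the event rates are cited ("Rates of hr-HPV infection and associated histologically proven disease were based on results from the HART study[9") but not given. Working backwards from n = [z₀.₉₇₅√(2p̄(1−p̄)) + z₀.₈₀√(p₁(1−p₁)+p₂(1−p₂))]²/(p₁−p₂)² with p₂ = 0.8p₁, n = 11,000 per arm gives 80% two-sided power at a control rate of about 3.1%, or some 343 control events. That concerns the comparisons the plan sized, not this one.

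**2. Women compared.** Control: 11,000 × 0.945 = 10,395. Intervention: 11,000 × 0.921 = 10,131. Expected control events at the four assumed risks are about 21, 31, 52 and 104.

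**3. Difference test on cumulative risk.** Exact conditional test of two Poisson counts, 2.5% per tail. Given the total count T, the intervention count under no difference is Binomial(T, w), with w = 10,131/(10,395 + 10,131) = 0.494. Power is summed over all counts with means 10,395p and 10,131p × RR.

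| Chance, by assumed p | 0.2% | 0.3% | 0.5% | 1.0% |
|---|---|---|---|---|
| 20% excess missed, full attendance | 93% | 91% | 86% | 75% |
| 50% excess missed, full attendance | 75% | 62% | 41% | 12% |
| 50% excess missed, 75% attendance | 81% | 72% | 54% | 23% |
| True ratio 0.5 called significantly better, full attendance | 39% | 57% | 81% | 98% |

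At full attendance, detection of a 50% excess reaches one half at about 0.37% by the normal approximation (about 39 control events). The exact test still detects only 49% at 0.4%.

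**4. What equal observed risks leave open.** Upper 95% limit of the risk ratio = exp[1.96√(1/E₁ + 1/E₂)]. At 0.5%: exp[1.96√(1/51.98 + 1/50.66)] = 1.47. At 0.2, 0.3 and 1.0% it is 1.84, 1.65 and 1.31.

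**5. Person-time rates, as the article specifies.** Assume about two years of exposure per control woman and four per intervention woman. Then w = 2 × 10,131/(10,395 + 2 × 10,131) = 0.661, and a cumulative ratio RR becomes a rate ratio RR/2.

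| Called significantly better, by assumed p | 0.2% | 0.3% | 0.5% | 1.0% |
|---|---|---|---|---|
| Equal cumulative risk | 54% | 73% | 92% | >99% |
| 20% cumulative excess | 34% | 50% | 73% | 96% |
| 50% cumulative excess | 14% | 20% | 32% | 58% |

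A 50% cumulative excess (rate ratio 0.75) is called significantly worse in about 0.1% of trials or fewer.

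**The case against.** **An article condenses, and the analysis plan is not shown.** A margin for a secondary comparison may well be set there. That limits the weight of the point. It does not remove it, because the article states an inferential rule for lesion rates and that rule does not answer the stated objective.

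**The misuse is not in the text.** A reader might infer that the plan will pass a non-significant result as acceptable. The document does not say so. The outcome is listed as rates, and the objective could be met by estimation. What stands is that no stated criterion prevents that reading.

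**Power is not uniformly poor.** A reader might also infer that any excess from 20% to 50% would usually be missed. That holds for 20% across the assumed range. For 50% it holds only below about 0.4% at full attendance; at 1.0%, 88% of trials would detect it.

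**The plan expects a much lower risk.** The Background expects long-term ≥ CIN3 risk after a negative hr-HPV test to be well below that after negative cytology. If the ≥ CIN2 ratio is 0.5, the difference test on cumulative risk shows significantly better in 39% to 98% of trials, and such a result settles the question without a margin. This is a fair point, but it leaves the intermediate ratios uncontrolled.

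**The cumulative-risk figures are not the analysis as written.** This is correct. On person-time the likely result is often significantly better rather than not significant. That makes the stated test less suited to this objective, because it can favour the longer interval when its cumulative risk is above the benchmark.

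**Conclusion.** The point holds in this form: the stated two-sided difference test does not fit the benchmark objective and does not control the error of accepting a four-year risk above the two-year cytology risk.

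Its size depends on a ≥ CIN2 risk the article does not give. Across 0.2% to 1.0%, at full attendance and on cumulative risk, the test misses a 20% excess in 75% to 93% of trials and a 50% excess in 12% to 75%. The person-time result further assumes about two and four years of exposure per woman.

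This is a secondary objective, and the full analysis plan may already set a criterion. The point should be corrected or clarified, but it does not touch the primary ≥ CIN3 comparison.

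**What to change.** For the interval objective only:

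- Compare cumulative ≥ CIN2 risk in entry-negative women, intervention at four years versus control at two years.
- Call the four-year risk within the benchmark only if the upper limit of the two-sided 95% confidence interval for the ratio or difference lies below a margin. The sponsor should justify that margin and fix it before exit data are opened.
- Do not take the 20% in the Sample Size section as the margin by default. It is a difference chosen for power in other comparisons, not a limit of acceptability.
- State that a non-significant difference is inconclusive and does not by itself support the longer interval.
- Keep the two-sided 5% test for the ≥ CIN3 comparison.

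The cost is wording and one confidence interval, with no extra women, visits or tests. The downside is that a tight margin may leave the question open unless the hr-HPV-negative risk is clearly below the benchmark. Under the same exact method with w = M × 10,131/(10,395 + M × 10,131), at 0.5% risk and full attendance, the chance of meeting the rule is:

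| Margin M | True ratio 0.5 | 0.8 | 1.0 |
|---|---|---|---|
| 1.2 | 95% | 46% | 13% |
| 1.25 | 97% | 54% | 18% |
| 1.5 | >99% | 83% | 50% |

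When the true ratio equals the margin, the rule is met wrongly in about 2% of trials. These margins are illustrations, not recommendations.
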